### Sample size calculation

The sample size estimation was conducted using G*Power (version 3.1) and based on detecting changes in the primary outcome of PA. Based on previous research, we anticipate the effect size for PA of d = 0.25 (an adjusted for the baseline of 5 min MVPA per day and assuming a standard deviation of MVPA of 17.8 minutes with a correlation of 0.59 between baseline and follow-up) [42]. We adjusted for clustering at the class level using a correction factor of [1 + (m—1) x ICC], where m represents the number of participants per class and ICC refers to the intraclass correlation coefficient for PA, assuming an average class size of 29 participating students, three classes per school and an ICC for PA of 0.034 [43]. Allowing for an expected dropout of 20% at the study endpoint, the required sample size to achieve 85% power with alpha levels set at 0.05 in 174 students (87 in the intervention group and 87 in the control group).

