### Statistical analyses

#### Analysis plan

Linear mixed models will be used to analyze the primary and secondary outcomes using IBM SPSS Statistics for Windows (version 20.0; 2010 SPSS Inc, IBM Company, Armonk, NY 2010 SPSS Inc., IBM Company, Armonk, NY), with significance set at p< 0.05. All analyses will subscribe to the intention-to-treat principle, whereby all participants will be included in the analysis in the group to which they were randomized. The models will be used to assess the effect of treatment, time and the group-by-time interaction, using random effects to account for the clustered nature of the data. Time and treatment will be included as fixed factors, with school class will be included as a random effect. According previous studies, school-level clustering is negligible after accounting for clustering at the class level [72]. However, if requerid, we will test this assumption and additionally adjust our analyses for school-level clustering. Mixed models are consistent with the intention-to-treat principle, assuming that data are missing at random. The analyses of the primary endpoint (ie, 24 weeks endpoint) will be performed using a repeated measures analysis of covariance applied using mixed linear models. Change from baseline to the postintervention of primary and secondary outcomes will be applied as the dependent variable, treatment (intervention or control), time (baseline and 24 weeks), and the group-by-time interaction will be included as independent variables. To examine the maintenance of the effect of the physical activity program on primary and secondary outcomes, comparable repeated measures approach will be used between group (intervention or control), time (baseline, 24 weeks and 48 weeks), and group-by-time interaction. Effect sizes between groups will be calculated using Cohen’s *d* (the adjusted difference between the control and intervention groups over time divided by the pooled standard deviation of change) and interpreted as follows: *d* = 0.2 (small), *d* = 0.5 (medium), and *d* = 0.8 (large). Potential moderators will be explored using linear mixed models with interaction terms for the following: sex (male, female), socioeconomic status (low, medium, high), and initial BMI status (healthy weight vs overweight/obese). Subgroup analyses will be only conducted if significant interaction effects P≤0.10. Sensitivity analyses will be performed (eg, multiple imputation and complete-case analysis). If the intervention effect estimate differs differs significantly from that obtained when these values are included, both results will be reported in the paper. For completeness in assessing the effect of missingness, we will also conduct one per-protocol analyses (ie, at the student levels). Therefore, our student-level per-protocol analysis, we will include only those students who participated at least 80% of sessions offered across the intervention period (up until our primary end point). Hypothesized mediators (Fig 2) of physical activity behavior change will be examined using structural equation modelling to assess the underlying causal pathways of the intervention.

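### The primary 24-week model contradicts itself: change from baseline is the outcome, yet baseline is a time level and the analysis of covariance lists no baseline covariate

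*Protocol article*

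**What the plan says.** All of this is in the protocol article, mostly under Statistical analyses, Analysis plan.

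- Type of analysis: the 24-week endpoint "will be performed using a repeated measures analysis of covariance applied using mixed linear models".
- Outcome: "Change from baseline to the postintervention of primary and secondary outcomes will be applied as the dependent variable".
- Fixed effects: treatment, "time (baseline and 24 weeks), and the group-by-time interaction will be included as independent variables". Baseline physical activity is not in the list.
- Random effects: the model is specified "with school class will be included as a random effect". School is a conditional addition: if needed, "we will test this assumption and additionally adjust our analyses for school-level clustering". No student effect or within-student covariance is named.
- Analysis population: intention to treat, "whereby all participants will be included in the analysis in the group to which they were randomized", with data assumed missing at random. Multiple imputation and complete-case analysis appear only as sensitivity analyses.
- Sample size calculation: the target difference is "an adjusted for the baseline of 5 min MVPA per day", with SD 17.8 minutes, baseline to follow-up correlation 0.59, class ICC 0.034, 29 students per class, 20% dropout and 174 students.

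**The concern.** A change from baseline to 24 weeks is one number per student. At baseline it is either undefined or zero for everyone, so a two-level time factor and a group-by-time term do not belong in a model for it. They belong in a model for the raw scores. An analysis of covariance, in turn, needs a baseline covariate, and none is listed.

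The text therefore leaves open whether the outcome is change or the raw score, and whether baseline is adjusted for. Each answer gives a different standard error for the primary outcome, so the analyst could choose after seeing the data. Under the literal reading, precision from baseline data already collected is given up, and students with one missing visit are lost.

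**Working it through.** **Inputs.** SD 17.8, r = 0.59, ICC 0.034, difference 5 min/day and 87 per arm come from the Sample size calculation. I assume equal SDs at both visits and a two-sided 5% test.

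**The plan's own figure.** The Analysis plan gives no variance to reproduce. The stated 174 does not follow from its inputs: the baseline-adjusted formula needs 149 per arm, 298 in total. With the design effect 1 + 28 × 0.034 = 1.952 and 20% dropout this becomes 298 × 1.952 / 0.8 ≈ 727. That is a separate matter; 87 per arm is used below only as the planned size.

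**Step 1: baseline adjustment.** In units of SD²:
- Unadjusted change: 2(1 − 0.59) = 0.82, so SD = 17.8 × √0.82 = 16.12 min.
- 24-week value adjusted for baseline: 1 − 0.59² = 0.652, so SD = 17.8 × √0.652 = 14.37 min.
- Ratio 0.82 / 0.652 = 1.26. Leaving baseline out is like discarding 1 − 1/1.26 ≈ 20% of students.

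**Step 2: literal fit with zeros at baseline.** The all-zero rows halve the pooled residual variance. The group-by-time SE is √(4 × ½ × 16.12² / 87) = 2.44, exactly the change-score SE, √(2 × 16.12² / 87) = 2.44. A simulation without clustering (4,000 runs) gave a type I error of 5.0%. The group contrast at 24 weeks from the same fit has SE √(2 × ½ × 16.12² / 87) = 1.73. This is too small by √2, and its simulated type I error was 17.4%.

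**Step 3: missing visits.** A change score needs both visits. At 20% dropout that is 0.2 × 174 ≈ 35 students left out unless values are imputed.

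**Step 4: raw scores with a class intercept only.** The two visits of a student are treated as independent, given class.
- Variance used: 4 × (1 − 0.034) = 3.864 SD² per student in each arm.
- Variance of the change-score comparison: 2 × 0.82 = 1.64.
- SE ratio √(3.864 / 1.64) = 1.53. Without clustering it is 1/√(1 − 0.59) = 1.56.
- Simulated without clustering at 87 per arm and a true effect of 5 min: power 16%, against 54% for change and 62% for baseline-adjusted analysis; type I error 0.3%.

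The ratio compares with a setting in which classes do not differ in their change. If they do, the excess shrinks. With ICC 0.034, three classes per arm and an assumed class-level correlation over time of 0.59, the model SE was 3.74 against an actual spread of 3.44, and type I error was 3.3%. In that setting, change and baseline-adjusted fits with no class term rejected in about 17% of null runs, so the class effect must stay in whichever model is chosen.

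**The case against.** The best defence is that the surrounding text points to an ordinary raw-score model. The section opens with treatment, time and their interaction, and the maintenance analysis repeats this over three visits. The sentence on change may be loose wording. Repeated measures can imply a within-student covariance, and the words analysis of covariance and the adjusted effect size suggest baseline adjustment. A journal article also leaves covariance structures to a fuller document. This has force against treating the omissions as faults in themselves. It does not remove the contradiction, because no fuller document could keep change as the outcome and baseline as a time level without altering one of them.

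Three stronger readings are tempting and should not be drawn:
- That the model cannot be fitted or biases the effect. Step 2 shows that a zero-filled fit runs and that, without clustering, its interaction test is a valid change-score test. The point estimate is unaffected by the wording.
- That the primary test has a type I error of 9–16%. This arises only if student correlation is added with a constant class intercept, which cancels from the group-by-time term. The difference in mean change then has true variance 0.0322 or 0.0453 SD² against 0.0236 assumed, at 69.6 students per arm. It rests on an assumed class autocorrelation of 0.8 or 0.5 and three classes per arm, neither of which the article states for the analysis.
- That the primary analysis is certainly complete-case. This holds only if change is literally the outcome and nothing is imputed. Listing complete-case analysis as a sensitivity analysis suggests otherwise.

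**Conclusion.** The primary 24-week analysis is specified inconsistently and needs one clear statement. Read literally, it is at best an unadjusted change-score comparison with about 26% more variance than the baseline-adjusted analysis assumed in the sample size. Without imputation it also excludes students missing a visit, contrary to the stated inclusion of everyone. Read as a raw-score model with class as the only random effect, the group-by-time standard error is about 1.5 times the change-score one.

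These two magnitudes belong to alternative readings and do not add up. The first depends on r = 0.59 and equal SDs. The second also depends on classes not differing in their change. The harm is to precision, to the standard error and to prespecification, not to the point estimate. The 9–16% type I error range is illustrative only.

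**What to change.** State one primary model. MVPA is taken as the measure because the trial is sized on it.

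- **Option (a):** MVPA at 24 weeks as outcome, baseline MVPA as covariate, treatment as fixed effect, class as random effect, no baseline time level. Change adjusted for baseline gives the same treatment estimate, so change may stay as the outcome if baseline is added. Since this option also loses students missing a visit, use multiple imputation in the primary analysis.
- **Option (b):** raw MVPA at all visits, treatment-by-time, a common baseline mean, a stated within-student covariance and a class random effect. This keeps students with one missing visit. A class intercept that is constant over time does not carry class differences in change, and this limit should be acknowledged.

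Extend the chosen model to 48 weeks for maintenance. Keep school-level adjustment as the plan's conditional step: 174 / 29 = 6 classes, so school and cluster-by-time effects may not be estimable.

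The cost is wording in the analysis plan and, under (a), moving imputation from sensitivity to primary analysis. No new data are needed.

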## Materials and methods

### Study design

The trial is registered in the protocol of clinical trials of the National Institute of Health clinicaltrials.gov (NCT05070377) on 7 October 2021 and approved by the human research ethics committee of the States University of Northen of Parana, Brazil (n° 4.452.513). The present study was written following Standard Protocol Items: Recommendations for Interventional Trials (SPIRIT) [41], which was aimed to improve the quality of clinical trial (S1 Checklist). The intervention will be evaluated using a two-arm randomized controlled trial with intervention and usual practice control groups. The assessments will be conducted at baseline, after 24-Weeks (primary endpoint) and after 48-Weeks from baseline (secondary endpoint). Baseline data collection will occur in the school term preceding the intervention (March 2022). The intervention will take place from April to October in public schools in Jacarezinho City. Post-test data collection (ie, 6-month follow-up) will start at the end of October and it will continue until midway through November, with the final following assessments (i.e., 12-month follow-up) being completed in April 2023.

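### The only between-arm test named for maintenance at 48 weeks is a three-visit group-by-time interaction, and a 24-week effect alone can make it significant

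*Protocol article*

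**What the plan says.** The Study design section has a third assessment "after 48-Weeks from baseline (secondary endpoint". The Analysis plan gives its purpose, "To examine the maintenance of the effect of the physical activity program on primary and secondary outcomes", and its method: a "comparable repeated measures approach will be used between group (intervention or control), time (baseline, 24 weeks and 48 weeks), and group-by-time interaction". The general rule for the models is "with significance set at p< 0.05".

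On model structure the plan says "Time and treatment will be included as fixed factors, with school class will be included as a random effect". It names no within-student covariance structure. Cohen's d is defined from an adjusted between-group difference over time, with no visit attached. The section names no between-arm contrast at 48 weeks and no criterion for when an effect counts as maintained.

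**The concern.** In the 24-week analysis there are two visits. The group-by-time interaction then has 1 df and is itself the between-arm difference in change, so testing it answers the question. The plan carries the same approach over to three visits. There the interaction has 2 df, and its null hypothesis is that the between-arm difference is the same at baseline, 24 and 48 weeks. An effect at 24 weeks alone breaks that null.

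Maintenance is a question about 48 weeks. The group main effect does not answer it either, because it averages over visits, baseline included. The interaction is thus the only named term that carries a between-arm difference in change, and it does not isolate the visit of interest. At stake is the secondary endpoint, which the Discussion presents as a strength of the trial: a significant interaction could be read as maintenance when the arms no longer differ at 48 weeks.

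**Working it through.** **Inputs**
- Effect: "an adjusted for the baseline of 5 min MVPA per day" (Sample size calculation).
- Variability: "assuming a standard deviation of MVPA of 17.8 minutes with a correlation of 0.59 between baseline and follow-up" (Sample size calculation).
- Numbers: 87 per arm planned. After the stated 20% dropout, 87 × 0.8 = 69.6, taken as 70.
- Design effect from the stated class size 29 and ICC 0.034: 1 + 28 × 0.034 = 1.952. The ICC is given for PA, not for change in PA, so results are shown with and without it.
- Significance level 0.05, taken as two-sided for 1-df contrasts.
- Assumed, because the protocol gives no figure: the correlations involving the 48-week visit. Equal correlations are taken first, then two decaying patterns.

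The protocol states no power figure for the maintenance analysis, so there is none to reproduce. Its total of 174 does not follow from its stated inputs. Baseline-adjusted analysis with 5/17.8, r = 0.59, 85% power and two-sided 0.05 needs 298 before clustering and dropout; 298 × 1.952 = 582, and 582/0.8 = 728. That is a separate matter: the equality shown below does not depend on n.

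**Step 1. Noncentrality under equal correlations and equal numbers per visit**

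ncp = (n/2) × Σ(d_t − mean d)² / [SD² × (1 − r)], referred to a noncentral chi-square with 2 df. Here d_t is the true between-arm difference at visit t.

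The denominator is 17.8² × 0.41 = 316.84 × 0.41 = 129.90.

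- Vanished, (0, 5, 0): mean 1.667; sum of squares 2.78 + 11.11 + 2.78 = 16.67.
- Fully kept, (0, 5, 5): mean 3.333; sum of squares 11.11 + 2.78 + 2.78 = 16.67.
- Half kept, (0, 5, 2.5): mean 2.5; sum of squares 6.25 + 6.25 + 0 = 12.5.

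In general the first two both equal (2/3) × δ². The equality therefore holds for any effect δ, SD, r, n or common design effect.

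**Step 2. Power of the 2-df interaction**

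| Setting | ncp, vanished and kept | Vanished | Fully kept |
|---|---|---|---|
| 87 per arm | 43.5 × 16.67/129.90 = 5.58 | 55% | 55% |
| 70 per arm | 35 × 16.67/129.90 = 4.49 | 46% | 46% |
| 70 per arm, design effect 1.952 | 4.49/1.952 = 2.30 | 25% | 25% |

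A half-kept effect at 70 per arm without design effect has ncp 35 × 12.5/129.90 = 3.37 and power 36%, lower than either extreme. A simulation of the ordinary repeated-measures F test (20,000 runs, 70 per arm) gave 45.1% vanished, 45.3% kept and 4.9% under the null.

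**Step 3. Correlation that decays over time (70 per arm, no design effect)**

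Let c be the pair of between-arm differences in change from baseline (at 24 and 48 weeks) and V their covariance matrix in SD² units. Then ncp = (n/2) × c′V⁻¹c / SD².

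Under AR(1) with r = 0.59, the baseline-to-48-week correlation is 0.59² = 0.348. The two change variances are 0.820 and 1.304, their covariance is 0.652, and the determinant is 0.644.

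- Vanished, c = (5, 0): 25 × 1.304/0.644 = 50.6; × 35/316.84 = 5.59; power 55%.
- Kept, c = (5, 5): 25 × 0.820/0.644 = 31.8; × 35/316.84 = 3.52; power 37%.

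If only the baseline-to-48-week correlation falls, to 0.49, the figures are 49% vanished and 41% kept.

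**Step 4. The 1-df contrast, between-arm difference in change from baseline to 48 weeks**

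Under equal correlations and 70 per arm, SE = √[2 × 316.84 × 0.41 × 2/70] = √7.42 = 2.72. For a fully kept effect, 5/2.72 = 1.84.

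| Setting | Vanished | Half kept | Fully kept |
|---|---|---|---|
| No design effect | 5% | 15% | 45% |
| Design effect 1.952 | 5% | 10% | 26% |

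This contrast separates kept from lost. The 2-df interaction does not.

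**The case against.** The strongest reply is that the plan lists model terms and does not lay down a decision rule. A reader might infer that maintenance will be declared when the overall interaction is significant, but the protocol does not say so. A 48-week contrast is available from the model described, nothing excludes it, and an analysis plan that is not shown could specify it. Between-group effect sizes are also promised, so reporting is not confined to one p-value. All of that stands, and for that reason the point is limited to what the interaction can and cannot show. It does not remove the point. The protocol states a specific approach for a named endpoint, the one relevant term it names does not match the stated question, and an analysis plan that followed the text faithfully would inherit the mismatch. The effect size is tied to no visit, so it does not settle 48 weeks.

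A second reply is that equal power for lost and kept effects rests on equal correlations and equal numbers per visit, which the protocol does not state. That is correct, and the equality should not be quoted without the condition. The decaying patterns checked move the result the wrong way, towards significance for a vanished effect.

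A third is that the preceding sentence takes change from baseline as the dependent variable, so the calculation on raw scores may not describe the intended model. This ambiguity is real. The maintenance sentence nevertheless lists baseline as a level of time, which makes three levels and a 2-df interaction. If only the two changes were modelled, the interaction would test whether the effect differs between 24 and 48 weeks. Its significance would then not indicate a remaining effect either.

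**Conclusion.** The point holds in this form: a significant three-visit interaction would not establish that an effect remains at 48 weeks, and the protocol names no contrast that would. With 5 min, SD 17.8 min, correlation 0.59 between all visits and equal numbers, the interaction is significant equally often for a vanished and a fully kept effect, between 25% and 55% of the time depending on numbers and clustering. With decaying correlation, vanished exceeds kept.

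Two stronger readings are not supported. The documents do not show that the trial will claim maintenance from the interaction alone, because no rule is written. Nor do they show a fault in the primary 24-week analysis, which has two visits and a 1-df interaction. The matter concerns the secondary endpoint. It deserves correction because it decides what can be concluded there, for the primary and the secondary outcomes alike.

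**What to change.** Add to the Analysis plan that maintenance is assessed by the between-arm difference in change from baseline to 48 weeks, estimated as a 1-df contrast from the same mixed model with a 95% CI and reported separately from the 24-week contrast. Add that the overall three-visit interaction p-value is not used to claim maintenance.

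The cost is a sentence or two of text. No new data, visits or model are needed. The gain is interpretability rather than power: under the assumptions above, with 70 per arm, a fully kept 5 min effect would reach significance at 48 weeks 26% to 45% of the time. The interval should therefore carry the conclusion, and a non-significant contrast should not be read as loss of the effect.

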### Primary outcome

#### Physical activity

Adolescents will be instructed to wear an Actigraph GT3X accelerometer on the hip at the height of the anterior iliac spine for all days (except when bathing, swimming, sleeping) for seven consecutive days. The subjects who use at least a wear time of >8 h on three days or more (including one weekend) will be included in the valid analyses data. The time (minutes/day) spent in physical activity of different light, moderate and vigorous intensities will be estimated, using validated cut-off points [52]. Non-wear time, defined as ≥60 min of continuous ‘0’ counts, will be removed from the data set [53]. Weekday and weekend days physical activity will be calculated separately (i.e., mean minutes per day).

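### Joint reporting of sensitivity and main results depends on an undefined significant difference, so a result that weakens the conclusion could go unreported

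*Protocol article*

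**What the plan says.** All of the relevant text is in the Analysis plan section of the protocol article.

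- Main model and its assumption: "Mixed models are consistent with the intention-to-treat principle, assuming that data are missing at random".
- Checks on it: "Sensitivity analyses will be performed (eg, multiple imputation and complete-case analysis").
- Reporting rule: "If the intervention effect estimate differs differs significantly from that obtained when these values are included", in which case "both results will be reported in the paper".
- A further analysis, not subject to that rule: "For completeness in assessing the effect of missingness, we will also conduct one per-protocol analyses", in which "we will include only those students who participated at least 80% of sessions offered across the intervention period".

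Two other sections show that missing primary-outcome data are expected. Sample size calculation: "Allowing for an expected dropout of 20% at the study endpoint". Physical activity, on which accelerometer records count: "wear time of >8 h on three days or more (including one weekend) will be included in the valid analyses data".

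**The concern.** A prespecified sensitivity analysis lets the reader see whether the conclusion survives a change in how missing data are handled. That works only if its result is shown whether or not it agrees with the main one. Here joint reporting depends on a finding of difference, and the finding is left to whoever applies the word *significantly* after seeing both estimates.

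The criterion is also the wrong one. The two estimates share most of their students, so they are strongly correlated, and failing to show a significant difference between them is not evidence that they agree. A sensitivity estimate could be smaller, with a confidence interval that crosses zero, and still not meet the condition.

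At stake is selective reporting on the primary outcome, in a trial that expects one student in five to be lost and that can lose further accelerometer data through the wear-time rule.

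**Working it through.** The plan gives no figure on this point, so there is none to reproduce. The check is whether the rule can be applied as written, followed by an illustration.

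**1. What the rule needs and what it has.**

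- Which two estimates are compared: not clear. *These values* has no antecedent. It could mean imputed values, students with incomplete follow-up, or accelerometer records that fail the wear-time rule (these candidates are my inference).
- What counts as a significant difference: no test or threshold. The section sets p < 0.05 for the outcome analyses, so a significance test is a natural reading, but the sentence does not say so.
- What is reported if the condition is not met: not stated. The natural implication is one result only.

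**2. Can a conclusion change on a small shift?** Inputs from Sample size calculation: 87 per arm, 20% dropout, 5 min/day, SD 17.8, baseline correlation 0.59. My assumptions: equal loss in both arms, no loss from the wear-time rule, no clustering, an observed effect of 5 min/day, the same standard error in both analyses, and a normal reference distribution.

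- Completers per arm: 87 × 0.8 = 69.6
- Baseline-adjusted SD: 17.8 × √(1 − 0.59²) = 14.37
- SE of the difference: 14.37 × √(2/69.6) = 2.44
- Main result: 5/2.44 = 2.05, p = 0.040
- Sensitivity estimate of 4.5: shift 0.5/2.44 = 0.21 SE, p = 0.065
- Sensitivity estimate of 4.0: shift 1.0/2.44 = 0.41 SE, p = 0.101

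A reduction of 10% or 20% therefore takes the result across 0.05.

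**3. Would the rule be triggered?** That depends on a choice the plan does not make.

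- If the overlap is respected, and complete cases are set against a two-visit mixed model for change, var(diff) = 2(1 − r)² × SD² × (1/n_c − 1/n) = 2 × 0.41² × 17.8² × (1/69.6 − 1/87) = 0.306. The SE is 0.55 and the 5% cut-off about 1.1 min. This model differs from the one in step 2, so compare the two only roughly.
- If the main model takes baseline as a covariate, the complete-case and main estimates are essentially the same, and there is almost nothing to test.
- If the overlap is ignored and the main SE is the yardstick, the cut-off is 1.96 × 2.44 = 4.78 min.

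Shifts of 0.5 and 1.0 min fall below both cut-offs, so neither would have to be reported. These cut-offs show only that the sentence does not determine a trigger. They do not measure the problem.

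**4. Dependence on the assumptions.** With the article's class-level design effect, 1 + (29 − 1) × 0.034 = 1.952, the SE becomes 2.44 × √1.952, about 3.4. An observed 5 min/day then has p = 0.142, so there is no significance to lose. The example would need a larger observed effect. The principle is unchanged: any result just past 1.96 SE can be moved back by a shift far smaller than 1.96 SE.

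**The case against.** **The sentence demands disclosure; it does not order suppression.** True. It requires both results when they disagree and is silent otherwise. The analyses will be run, and a large discrepancy would be reported. So the most the text supports is that a weakening result *could* go unreported, not that it would.

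***Significantly* may mean materially.** Possible. The rule would then rest on judgement after the data are seen, with no stated margin, so the defect remains.

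**Other commitments cover the gap.** The per-protocol analysis is unconditional, but it selects students on session attendance. That is adherence, not missing outcome data, and control schools continue usual practice with no programme sessions to attend. The pledge under Patient and public involvement to publish whatever the direction or magnitude concerns the trial's findings in general. The data set promised under Data management comes up to three years after the last assessment. Neither puts the sensitivity results in the paper.

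**The named analyses will probably lie close to the main one.** This stands, and it limits the likely harm. It also means that reporting them costs little.

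Two stronger readings are tempting, and the document supports neither.

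- A reader might infer that the set of analyses cannot challenge missing at random, so that fragility is bound to stay hidden. Standard multiple imputation does share the mixed model's assumption, and complete-case analysis generally needs a stricter one. But the list is introduced as examples, and a missing-not-at-random analysis is commonly left to the SAP, which is not shown. Its absence from a condensed article is no finding.
- A reader might want to state in minutes how large a shift would be missed, starting from the stated power: 5/3.0 = 1.67 as the SE. That power already allows for 20% dropout, so inflating this SE again for missing data counts dropout twice. Comparing complete cases with a full data set also uses data nobody will have.

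**Conclusion.** The point holds as a defect in a stated reporting rule. The Analysis plan makes joint reporting of sensitivity and main results conditional on a significant difference, without defining the test, the threshold or the values concerned. Because a non-significant difference between overlapping estimates does not show robustness, a sensitivity result that materially weakens the primary conclusion could be left out while the plan is followed to the letter.

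The size cannot be put as one number, because the comparison is undefined. The illustration shows only that shifts of 0.21 to 0.41 standard errors can move a result from p = 0.040 to 0.065 or 0.101, under the assumptions listed with it. The conclusion rests on the wording and does not need those figures. It is a reporting fault worth correcting before analysis; it does not invalidate the main model.

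**What to change.** In the Analysis plan:

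1. Delete the condition that the estimate must differ significantly.
2. Commit to reporting every planned sensitivity analysis (multiple imputation and complete-case, plus any other that is prespecified) with its estimate and 95% CI beside the main result, whatever the difference.
3. State what *these values* refers to, so that the comparison is identifiable.

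The analyses are already planned, so the cost is a sentence or two and one supplementary table. A delta-adjusted multiple imputation would be a useful optional addition, at the cost of choosing and justifying a delta range; the correction does not depend on it.
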